P_1_ = 62% i.e. the proportion of the participants in the unexposed (control) group who are either moderately or vigorously physically active *(58.8% engaged in moderate physical activity levels while 3.2% engaged in high physical activity levels based on the study by Odunaiya, et al., 2010)* [12].

P_2_ = 72% i.e. the proportion of the participants in the exposed (experimental) group who are expected to become physically active 12 weeks after the intervention. This translates to the effect size i.e. 10% increase in the outcome measure of physical activity at follow up [24].

*ρ* = 0.38 [30].

The design effect or variance inflator factor = [1+ (k-1) x*ρ*

k = approximately the average number of individuals to be sampled per cluster. This will be 50 per school.

Three hundred and thirty six per group is the minimum sample size needed to detect whether the stated difference exists between the two proportions. A total of one thousand in-school adolescents will be selected for the study (500 for the control and 500 for the experimental group) to account for loss to attrition and increase the precision for the point estimate for physical activity behaviours among the adolescents.

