### Data collection

The data collection will be at three time points the first will be at baseline (T0), the second will be immediately after the 12-week intervention (T1) while the third will be three months after the intervention (T2). Details in Table 1. The data collection will employ a mixed methods approach including:(i)A desk review of relevant state and national NCDs prevention policies and guidelines on physical activity and an assessment of the level of coherence of the School Health Promotion policy with these policies. Other documents which will be reviewed include the Physical Health Education curriculum and school timetable to assess the opportunities for PA during school hours. The policies which regulate the construction of schools will also be reviewed to assess the extent to which these documents regulates or influences the built environment and physical activity levels in school.(ii)Physical and Health Education Teachers will complete the School Physical Activity Policy Assessment tool (S-PAPA) – a standardised semi-structured tool which assesses physical education, recess and other physical activity opportunities before, during and after school [31]. For this study, only two components will be assessed - physical education and recess. Scores on the S-PAPA tool will be tabulated based on policies and practices identified as being related to children’s physical activity during school [32, 33]. Total point scores will also be either median-split into high- and low or stratified by percentile for analysis [34].(iii) Focus Group Discussions and In-depth interviews will be held with teachers and school principals respectively to assess their opinion about social norms and support and the extent of implementation of physical activity policies and programmes in schools, level of funding, and the frequency of engagement in structured physical activity. Observations will be conducted to document facilities for physical activity in the schools using the Sport, Physical Activity and Eating behaviour: Environmental Determinants in Young people (SPEEDY) checklist. The SPEEDY checklist measures the built environment of schools and can be scored to quantify environmental support for physical activity [35]. The checklist assesses school-level environmental variables such as *Walking Provision, Cycling Provision, Aesthetics, Sport and facility provision, Other facility and Design of the school grounds* [36] The scores from each of the key variables will be dichotomised into low and high based on percentiles, and the school physical activity suitability index will be computed [36, 37].(iv) A cross sectional survey will be conducted among the students using an adapted version of the *Physical Activity Questionnaire for Adolescents (PAQ-A)* [38] to generate self-reported data on the level of physical activity among young people. The PAQ-A is a self-administered, 7-day recall instrument. It was developed to assess general levels of physical activity for high school students approximately 13 to 19 years of age. It assesses the frequency of participation in physical activity during spare time, physical education period, lunchtime, after school, in the evenings and on weekends. A summary of the physical activity score is generated from the mean of 8 items, and ranges from 1 to 5, with higher scores indicating more frequent participation in physical activity [38]). The physical activity levels will be categorised into three; low physical activity level will be those who score between 1 to 1.9 while moderate and high physical activity levels will be those who score between 2 to 3.9 and 4 to 5 respectively [13]. For some statistical analyses, the self-reported physical activity level will be treated as a continuous variable. In a study to establish the convergent validity of the PAQ-A, the instrument was found to be significantly correlated to all self-report measures (including activity rating, *r* = 0.73; Leisure Time Exercise Questionnaire, *r* = 0.57; and 7-day physical activity recall interview, *r* = 0.59) [39]. The survey will also assess the frequency of engagement in structured physical activity from two time points (baseline and follow up) as the primary outcome measure. Based on the theory of Planned Behaviours which is the theoretical framework guiding this intervention, other variables which will be incorporated into the Physical Activity Questionnaire for Adolescents (PAQ-A) are the measures for attitude, subjective norms, perceived behavioural control and self-efficacy. A research tool which was theoretically derived by Motl et al., 2000 based on Theory of Reasoned Action (TRA) and Planned Behaviour (TPB) and Social-Cognitive Theory (SCT) will be used to assess the social-cognitive factors among this young people. This questionnaire has been tested and evidence provided for its factorial validity as a unidimensional measure of attitudes, subjective norms, perceived behavioural control and self-efficacy about physical activity among adolescent girls [40]. The core variables i.e. *knowledge of health benefits of physical activity, attitude, subjective norms, perceived behavioural control and self-efficacy about physical activity* will be analysed by scoring and summing up all question items and cut-offs will be determined using percentiles.The survey will be complemented with focus group discussions to assess their opinions about the individual, social, community, institutional and policy factors which influences the physical activity behaviours of young people.(v)Anthropometric and other physical measurements (body-mass-index for age, waist-to-hip ratio, blood pressure) will be documented. Anthropometric measurements will be taken twice and averaged; for discrepancy >10%, a third measurement will be taken. The height and weight will be assessed using standard anthropometric procedures. Height will be measured using a portable height meter/stadiometer. Students will be asked to take off their shoes and stand with their back to the portable height meter/stadiometer. The sliding bar will be lowered and pressed flat on the head and recorded to the nearest centimeter. Body weight will be measured using a digital scale and weight will be recorded to the nearest gram. Age -and sex -specific prevalence of overweight and obesity will be determined by the body-mass- index for age Z scores using the criteria defined by the World Health Organisation (WHO). According to the WHO cut off points; overweight is considered to be > + 1SD (equivalent to BMI 25 kg/m2 at 19 years), Obesity: > + 2SD (equivalent to BMI 30 kg/m2 at 19 years), Thinness: <-2SD, Severe thinness: < −3SD and Normal: > −1 to < +1 SD. Standard deviations (Z-scores) will be computed using the World Health Organisation (WHO) reference population, 2007 soft ware (Anthropometric Software Program, Version 1.0.4 [41]. Blood pressure will be measured and the mean of three measurements will be recorded. Referrals will be initiated for children whose blood pressure exceeds the 95th percentile for age. Waist circumference will be measured to the nearest 0.1 cm horizontally at the narrowest point between the lower end of the rib cage and iliac crest. Hip circumference will be measured to the nearest 0.1 cm, at the greatest horizontal circumference below the iliac crest at the level of greater trochanter. Waist hip ratio will be obtained as waist circumference/hip circumference.The fitness level of the adolescents will be measured using the 20-m shuttle run test (20-mSRT) also known as the multi-stage fitness test. The 20-mSRT is the most widely used field-based test for aerobic fitness in young people and UK percentile data and health-related cut points are available [42]. A systematic review recently concluded that the 20-mSRT is the most reliable and valid field based method to estimate aerobic fitness in young people [43]. Performance in the 20-mSRT is typically expressed as laps, levels or distance completed. The 20mSRT estimates the cardiorespiratory fitness (aerobic capacity). Children run back and forth between two lines 20-m apart following beep signals played from a pre-recorded CD. The pace of the test is ramped such that running speed increases by 0.5 km/h each minute or period. The test is finished when the child stops owing to fatigue or when he/she does not reach the line in time with the audio signal on two consecutive occasions [44]. The last completed run indicates the final result of the test. The physical fitness data will be analysed and used as continuous variables and an increase in test results will indicate higher physical fitness [45].(vi) Step count will be recorded using a pedometer. During the data collection process, 100 students (10% of the sample) will be asked to wear a Yamax SW200 Step Digi-Walker pedometer on their right hand for seven consecutive days, except during sleep and water based activities. Text messages/phone calls will be made daily as reminders to ensure compliance. The pedometers will be sealed with a sticker or cable to prevent reactivity i.e. a situation where individual change their normal activity pattern as a result of being monitored.The pedometers will be worn daily for seven days with a minimum of 4 valid days. Step counts of less than 1000 steps per day and greater than 30,000 steps per day will be treated as missing data [46]. Step count of 10,000 to 11,700 and over will be recorded as achieving the daily recommended levels of 60 min of MVPA in adolescents [47].

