### Primary outcome measurements

The primary outcome measures will be documented at baseline and final evaluation/follow-up. This include(i)Self-reported physical activity levels among the students using the International Physical Activity Questionnaire for Adolescents(ii)Step count recorded using a pedometer

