#### Intervention phase

The findings of the research phase will guide the development of the multi-level intervention targeting the policy makers, officials of the Ministries of Education, Health, Youths and Sports, School Heads and Physical and Health Education Teachers and the students. A *multilevel intervention is defined as an intervention* that addresses at least three levels of the multilayer system. It target at least three sources of influence that may ultimately result in improved health behaviour and outcomes [25]. Suggested activities which were identified based on literature [24, 48, 49] are outlined in Table 3.

**Table 3 Tab3:** A list of multi-level Interventions based on a review of literature

Level	Possible Activities/Interventions
Individual Level	• Educational materials for students • Special Dance events in schools • Debates and other co-curricula activities • Experience sharing by role models/athletes • M health –SMS • Peer Education
Socio Cultural level	• Dialogue and dissemination meetings with Parent Teachers Association, Teachers, Principals
Built Environment	• Provision/Refurbishment of PA facilities
Policy/Institutional Level	• Development of curriculum &Training of Teachers • Review of PE Curriculum • Creating and training a school-based action team or small groups or committees. • Dissemination Meetings, • Production of evidence based dissemination materials – policy briefs, fact sheets etc. • One – on -one Advocacy visits • Celebration of special days and events

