#### Data management and statistical analysis

Serial numbers will be assigned to the questionnaires for easy identification and recall of the instrument and these will be stored in a place safe. A coding guide will be developed and sections of the tools which are open ended will be coded before data entry. The data will be cleaned to identify and correct all errors. The quantitative data will be analyzed using STATA version 13.

There are two key primary outcome variables specifically step count measured with pedometers which is a continuous outcome variable and self-reported physical activity level which can be a continuos or ordered categorical variable, details in Table 4.

**Table 4 Tab4:** Description of outcome Measures

	Description of outcome measures	Type of Variable
Primary Outcome Measures	Self-reported physical activity score/levels	Continuous
		Ordered categorical
	Step count (average steps/day)	Continuous
Secondary Outcome Measures	Anthropometric Measurements (measured using body mass index)	Ordered categorical
	Fitness level measured using the 20-mSRT	Ordered categorical
	Knowledge of the health benefits of physical activity	Ordered categorical
	Attitude toward Physical activity	Ordered categorical
	Self efficacy	Ordered categorical
	Perceived behavioural control and intention	Ordered categorical
	Social Norms and Social support,	Ordered categorical
	Policy or programme changes	Qualitative

At baseline, bivariate analysis (cross tabulation) will be used to compare the differences in proportions of the primary and secondary outcome measures of the experimental and control groups. Chi-square test (X^2^) will be used for significance testing of the self-reported physical activity levels (dependent ordered categorical variable) and other categorical independent variables while repeated measures ANOVA will be used for Step count (average steps/day). Based on data generated using bivariate analysis, all independent variables which are significant at 10% will be incorporated into the regression model.

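### The pedometer behind a primary outcome is to be worn on the right hand, with no justification and no evidence that the plan's step-count rules hold at that site

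*Protocol article*

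**What the plan says.** Item (vi) of the Data collection section says that 100 students, 10% of the sample, "will be asked to wear a Yamax SW200 Step Digi-Walker pedometer on their right hand for seven consecutive days". The device stays on during waking hours apart from water activities, and at least four valid days are required.

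The same item fixes how the readings are used. For data cleaning: "Step counts of less than 1000 steps per day and greater than 30,000 steps per day will be treated as missing data". For classification: "Step count of 10,000 to 11,700 and over will be recorded as achieving the daily recommended levels of 60 min of MVPA in adolescents". Both rules are cited to outside references (46 and 47).

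The Primary outcome measurements section lists "Step count recorded using a pedometer" as the second of two primary outcomes. The analysis section confirms this: "There are two key primary outcome variables specifically step count measured with pedometers which is a continuous outcome variable". Tables 2 and 4 define the variable as average steps per day, and Tables 1 and 2 schedule it at T0, T1 and T2.

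No other section mentions a wear site, a validation of hand wear, or a conversion from hand-worn counts to steps.

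**The concern.** The instruction fixes where a primary outcome is measured, and the text gives no reason for the choice. A body-worn motion counter responds to movement at the point of attachment. A school pupil's right hand moves a good deal without a step (writing, gesturing, throwing) and can be nearly still during steps (carrying a bag). A hand-worn count is therefore a mixture, yet the plan handles it as a plain step count.

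Step count is the only objective primary outcome. The other is self-report, in a trial whose control schools receive no intervention and whose text describes no blinding of students. If the pedometer reading is hard to interpret, the primary evidence rests mainly on the questionnaire.

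The problem cannot be repaired later. Without counts from another site on the same days, no analysis can turn hand counts into steps. Changing the site after T0 would break comparability with T1 and T2.

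**Working it through.** The plan states no figure for measurement error, so there is none to reproduce. The check has four steps.

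**1. Extent.** Inputs: 1,000 students in total (Sample size section); 100 pedometer wearers (Data collection); three time points (Tables 1 and 2). 100 / 1,000 = 10%, as the protocol states. 100 × 3 = 300 wear-weeks at most, before dropout and invalid days. The instruction covers all of them.

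**2. What a hand-worn count contains.** For one student on one day, let S be true steps, A hand movements counted without a step, and M steps missed because the hand was still. The recorded count is

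H = S + A − M, so the error is H − S = A − M.

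A and M act in opposite directions and the documents give neither. Both the sign and the size of the error are therefore unknown.

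**3. Effect on the comparison of arms.** Writing Δ for the difference between arms in means,

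ΔH = ΔS + (ΔA − ΔM).

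- *A and M have the same mean in both arms.* The last term is zero and the contrast is unbiased on average. Day-to-day and student-to-student variation in A and M still enters the data, in a subset of only 100.
- *A constant share m of steps is missed in both arms, and A is unrelated to S and alike in both arms.* Then H = (1 − m)S + A and ΔH = (1 − m)ΔS. The raw difference shrinks. The standardised difference becomes (1 − m)ΔS / √[(1 − m)²Var(S) + Var(A)], which is smaller in size than ΔS / √Var(S) whenever Var(A) > 0 and ΔS is not zero.
- *The intervention changes the type of activity.* Then ΔA − ΔM need not be zero, and the contrast can be biased either way. Table 3 of the Intervention phase section lists "Special Dance events in schools" among possible activities, so such a change is conceivable. It is not established.

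Using one site in both arms equalises placement. It does not equalise the mix of activities.

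**4. The step rules.** The daily limits of 1,000 and 30,000, and the band of 10,000 to 11,700 and over, are applied to H. The protocol does not say at which body site references 46 and 47 derived them, and it offers no evidence that H and S agree well enough for the rules to carry over. The limits remove only extreme days, so a moderate miscount within them passes unnoticed.

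**The case against.** The strongest reply is that the protocol does not describe how this device works or where it is meant to be worn, so a claim about its mechanism would be outside knowledge. That stands for the device's specifics. The concern needs only the general point that a motion counter registers movement where it is attached.

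A reader might infer several stronger things, which the documents do not support:

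- *That the device records arm movement instead of steps.* This is too absolute, because arm swing accompanies walking. Miscounting of unknown size is what can be defended.
- *That the step cut-offs are invalid at the hand.* Their sources are not available. What can be said is that the plan does not show that they hold. The primary variable is also continuous average steps per day, so a student crossing the 60-minute cut-off by error affects a derived classification and not the main comparison.
- *That the outcome is biased between arms through dance.* Dance is only under consideration. T1 follows the intervention and T2 comes three months later, so dance events need not fall in a wear week. Dance also involves steps.
- *That the pedometer is the only check on self-report.* The shuttle run, anthropometry and blood pressure are also measured on students. Step count is the only objective measure among the primary outcomes.
- *That a percentage can be put on the miscount.* The documents contain no comparison of hand with another site, so any such figure would be invented.

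Finally, the phrase may be a slip in a condensed article, for example for the right-hand side of the body. The text cannot settle this. As published, though, it is an explicit fitting instruction, and staff who follow it would put the device on the hand.

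**Conclusion.** The point holds in a limited form. The protocol places the pedometer for a primary outcome on the right hand without justification, validation or correction elsewhere. Counts from that site mix arm movement with steps and can miss steps.

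The extent is all pedometer data, up to 300 wear-weeks. The size and direction of the error cannot be derived from the documents. Likely consequences are added noise and possible dilution of the contrast in a 100-student subset. A difference in error between arms is possible, but only if the intervention changes the kind of activity during wear weeks. Use of the daily limits and the 60-minute cut-off at this site is unsupported, not shown to be wrong.

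The conclusion assumes that the text will be followed as written and that the counter responds to motion at its point of attachment. It should be settled before baseline, because hand counts cannot be converted afterwards.

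**What to change.** Before T0, replace the right-hand instruction in item (vi) of Data collection with a trunk site, the waistband at the right hip. The protocol itself does not name this position, so confirm it against the device instructions and against the wear site used in references 46 and 47. If hand wear is truly intended, give the evidence for it and for applying the daily limits and the 60-minute cut-off at that site.

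State that the same site applies at T0, T1 and T2 in both arms. Have the research assistants check the position at fitting, and repeat it in the daily reminder that students already receive.

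The cost is a line or two in the measurement procedure and a short addition to assistant training. The device, students and visits stay the same.

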### Primary outcome measurements

The primary outcome measures will be documented at baseline and final evaluation/follow-up. This include(i)Self-reported physical activity levels among the students using the International Physical Activity Questionnaire for Adolescents(ii)Step count recorded using a pedometer

### Secondary outcome measures

Secondary measures which will be documented are fitness levels, anthropometric and physical measurements, knowledge of the *health benefits of physical activity, attitude, self efficacy, perceived behavioural control and intention, Social Norms, Social support, policy or programme changes* on PA. Details in Table 2.

**Table 2 Tab2:** Data elements to be collected, study timepoints (T0, T1, T2) target groups

Description of outcome measures	Method	Type of variable	Timing	Target group
Demographic characteristics, Socio-economic status	Questionnaire	Ordered categorical	T_0_ T_1_ T_2_	Adolescents
Knowledge, attitude, beliefs on nutrition and PA	Questionnaire	Ordered categorical	T_0_ T_1_ T_2_	Adolescents
Self-reported physical activity levels	Physical Activity Questionnaire (PAQ –A) for adolescents	Continuos	T_0_ T_1_ T_2_	Adolescents
		Ordered categorical		
PA Self efficacy	Questionnaire	Ordered categorical	T_0_ T_1_ T_2_	Adolescents
Perceived behavioural control and intention	Questionnaire	Ordered categorical	T_0_ T_1_ T_2_	Adolescents
Fitness level measured using the 20-mSRT	20-mSRT	Ordered categorical	T_0_ T_1_ T_2_	Adolescents
Step count (average steps/day)	Pedometers	Continuous	T_0_ T_1_ T_2_	Adolescents
Anthropometric and Physical assessments (BP, Ht, Wgt, BMI)	Brief physical assessment	Continuous	T_0_ T_1_ T_2_	Adolescents
Social Norms and Social support,	Questionnaire	Ordered categorical	T_0_ T_1_ T_2_	Adolescents, Teachers, School Heads
Built environment	Observation and checklist	Ordered categorical	T_0_	School Environment
Policy or programme changes	Key Informant interviews	Qualitative	T_0_ T_1_ T_2_	School Heads, Officials of Govt. and Ministries Policy Makers,

